### Outcome measures

Table 1 outlines the SPIRIT schedule, which summarises the schedule of enrolment, interventions, and assessments.

**Table 1 Tab1:**
[figure not shown]
PACeR trial schedule of enrolment, interventions, and assessments adapted from original table© SPIRIT Group [48]

A CPR with established diagnostic accuracy is used to confirm the presence of CR [28]. This involves 4 physical tests, which include measurement of cervical rotation and Upper Limb Neurodynamic Test (ULNT) 1. Cervical rotation range is measured with a CROM 3 device (Performance Attainment Associates, USA) made up of 3 cervical inclinometers. Reliability (ICC = 0.89–0.90) and construct validity of the CROM have been demonstrated [38]. ULNT 1 is a validated pain provocation test for nerve tissue [21, 22], which has also demonstrated moderate reliability (kappa = 0.45) [39].

Participants undergo the following outcome measures at baseline, 4 and 12 weeks:

The *Neck Disability Index* is a ten-item self-reported questionnaire that assesses pain and associated disability [13]. The NDI is valid and reliable for use in cervical radiculopathy [40]. The Taskforce on Neck Pain considered it to be the most responsive self-assessment questionnaire available [41] due to its ability to discriminate between clinical improvement and deterioration in neck pain [42].

The *Numerical Pain Rating Scale,* a reliable and responsive [43] generic measure of pain [14] is being used to measure both neck and arm pain.

Cervical *range of motion* measured with a CROM 3 device (Performance Attainment Associates, USA). Flexion, extension, side flexion and rotation, along with symptom response, is being measured.

The *SF-12 Health Survey* questionnaire will be used as a measure of quality of life (QoL) and is a practical, reliable, and valid measure of physical and mental health [44, 45].

The *Hospital Anxiety and Depression Scale (HADS)* and the *Fear Avoidance Belief Questionnaire (FABQ)* are used as psychosocial measures. The HADS [16] was developed as a tool to identify anxiety and depression in patients attending non-psychiatric hospital outpatient clinics and has been validated [46]. The FABQ was initially established to measure how patients’ beliefs about physical activity and work affected their low back pain [17]. FABQ has also been shown to predict prolonged disability in neck pain patients, making it appropriate to use with this cohort of neck pain patients [18].

*Pressure Pain Threshold* (PPT) is measured using pressure algometry and provides a measure of mechanosensitivity of the nervous system [20]. Good inter and intra-rater reliability of PPT has been established in a neck pain cohort [20]. A similar profile of altered mechanosensitivity previously found in Whiplash Associated Disorder (WAD) patients, has also been identified in patients with chronic cervical radiculopathy [47]. PPT is measured using the SENSEBox algometer (Somedic, Sweden) with a 1cm^2^ head, applied at a rate of 30 kPa/sec, at standardised sites (dermatomal key points and maximal pain area) bilaterally, and on the right anterior tibia. The mean of 3 measurements at each site, recorded at 10 s intervals, and a random site order is applied.

Intra-rater reliability of the PI will be verified for the ULNT 1 and PPT measurements by conducting repeat tests for 10 participants. Intraclass Correlation Coefficients (ICC) will be calculated using a one-way random effect model (for consistency agreement).

*PainDETECT,* a self-report questionnaire to detect neuropathic pain components, originally designed for use in low back pain [23] is also being used at baseline. This questionnaire has excellent test-retest reliability (ICC = 0.93), good internal consistency (Cronbach’s alpha > 0.83) and high sensitivity, specificity and positive predictive value (> 80%) [23].

Participants’ overall rating of recovery is assessed using the *Global Rating of Change scale* (GROC) [19] at 4 and 12 week follow-up.

A final phone follow-up at 6 months will capture GROC, NPRS, NDI and any additional treatment received.

In addition to these outcome measures, baseline demographics including co-morbidities, educational level, smoking status, occupation and work status will also be captured; with change in work status noted at subsequent time points.

Medication use for both groups is recorded weekly over the first month by physiotherapists and by the PI at follow up assessments. Adherence to home exercise prescription is also recorded on a weekly basis in the MP group and again at the 12 week assessment. The number of treatment sessions attended by participants will also serve as an additional measure of treatment adherence.

### Randomisation

The allocation sequence has been generated by an independent academic colleague using a computer-generated list of random numbers and randomly varied block sizes of 4 and 6 from www.randomization.com. The allocation sequence is concealed from the PI, who enrols and consents participants. The PI informs the randomiser when a new participant has been enrolled and once randomised, the randomiser directly informs the relevant physiotherapist, who informs the participant of their group allocation by phone. Participants are randomly assigned using a 1:1 group allocation ratio. The PI is blinded to group allocation until the 12 week assessment. Given the nature of the interventions, it is not possible to blind the participants or therapists involved in providing either intervention.

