**Methods:**

Participants are recruited from GP referrals in an urban setting, from a neurosurgery non-urgent waiting list and from self-referral through Facebook advertising. Eligible participants (*n* = 64) are diagnosed with radiculopathy based on a clinical prediction rule and must have symptoms of unilateral, single level, radiculopathy for between 2 and 12 weeks, without having yet received physiotherapy. Random 1:1 group allocation (using variable block sizes), allocation concealment, blinded assessment and intention to treat analysis are being employed. Treatment is provided by clinical specialist physiotherapists in primary and secondary care settings. Outcomes are measured at baseline, 4 (primary endpoint) and 12 weeks. Participants’ report of pain, disability and their rating of recovery is also recorded by telephone interview at 6 months. Statistical analysis of between group differences will be performed with ANOVAs and MANOVAs, and multivariable regression analysis will be undertaken to explore predictor variables. Ethical approval for this study has been received from the Beaumont Hospital and Irish College of General Practitioners Research Ethics Committees. The trial is registered at ClinicalTrials.gov (NCT02449200).

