## Methods

### Study design

The PACeR trial is an exploratory, two parallel group, assessor-blinded, multi-centre randomised controlled trial, with a primary endpoint of pain and disability at 4 weeks. This is a superiority trial to investigate a novel, complex physiotherapy intervention using allocation concealment, blocked randomisation and a 1:1 allocation ratio. The SPIRIT statement and CONSORT guidelines are guiding the reporting and conduct of the study [24, 25]. Ethical approval for this study has been granted by the medical research ethics committees of Beaumont Hospital (REC ref. 14/85), the Irish College of General Practitioners (ICGP) and the Royal College of Surgeons in Ireland (RCSI). Recruitment is via GP referral, self-referral through social media advertising, and initially, also from a waiting list of non-urgent referrals to a national neurosurgery centre. Five clinical centres (1 hospital and 4 private practices) are currently providing the trial’s interventions. Physiotherapy is provided by postgraduate master’s level or clinical specialist musculoskeletal physiotherapists.

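### The trial is called assessor-blinded without limit, but the stated blind leaves the 12-week physical measures ambiguous and does not reach the 6-month interview

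*Protocol article*

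**What the plan says.** The claim of blinding is general. Study design states: "The PACeR trial is an exploratory, two parallel group, assessor-blinded, multi-centre randomised controlled trial, with a primary endpoint of pain and disability at 4 weeks". The Abstract (Methods) adds that "allocation concealment, blinded assessment and intention to treat analysis are being employed". Neither ties blinding to particular visits.

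The duration is given once, under Randomisation: "The PI is blinded to group allocation until the 12 week assessment". The same section says that participants and therapists cannot be blinded.

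Outcome measures shows who examines: "Intra-rater reliability of the PI will be verified for the ULNT 1 and PPT measurements by conducting repeat tests for 10 participants". It also places the PI at the later visits: "Medication use for both groups is recorded weekly over the first month by physiotherapists and by the PI at follow up assessments".

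Two further sentences in Outcome measures bear on the later time points. On adherence: "Adherence to home exercise prescription is also recorded on a weekly basis in the MP group and again at the 12 week assessment". On the last contact: "A final phone follow-up at 6 months will capture GROC, NPRS, NDI and any additional treatment received". The Abstract describes that last contact as a telephone interview. Interventions adds that control participants are offered treatment at 12 weeks.

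**The concern.** An assessor-blinded label tells readers that whoever measures the outcome does not know the arm. Here the label covers the whole trial, while the rule behind it stops at or around the second of three follow-up contacts.

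This matters most for outcomes that depend on the examiner. For range of motion, pressure pain threshold and ULNT 1, the examiner sets the end of movement, applies the pressure or judges the response. The article itself reports only moderate reliability for ULNT 1 (kappa 0.45), so there is room for expectation to influence the result. NDI, NPRS and GROC are the participant's own report. When they are taken by interview, though, the way a question is put and an answer recorded can still be shaped by knowledge of the arm.

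At stake is detection bias in secondary outcomes, and a published description of blinding that is wider than the procedure supports.

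**Working it through.** No arithmetic decides this point. The check is to set the claim, the rule and the visit content side by side.

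**Step 1. Is the PI the assessor?** The article does not say so in one sentence. However, the reliability check for ULNT 1 and pressure pain threshold is on the PI's own repeat measurements, and the PI records medication at follow-up assessments. Physiotherapists' recording of medication is confined to the first month. The PI is the only staff member whom the text places at follow-up assessments. That the PI is the examiner is a strong inference, and it is used below.

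**Step 2. What is measured, and when?** Aims sets the physical measures (range of motion, pressure pain threshold, ULNT 1) and most questionnaires at 4 and 12 weeks. NDI, NPRS and GROC are taken again at 6 months.

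**Step 3. Apply the rule under both readings of the word until.**

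| Contact | Outcomes | Blind ends as the 12-week visit begins | Blind ends when the 12-week visit is complete |
|---|---|---|---|
| 4 weeks (primary) | self-report and physical | covered | covered |
| 12 weeks | self-report and physical | not covered | covered by the rule, but open to disclosure within the visit |
| 6 months | NDI, NPRS, GROC by telephone | not covered | not covered |

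Only the 12-week row depends on the reading. Taking 6 months as about 26 weeks, the last contact falls about 26 − 12 = 14 weeks after the stated blind ends.

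**Step 4. What could disclose allocation at 12 weeks?**
- Only the physiotherapy arm receives the exercise programme, and that arm is advised to continue it up to this assessment. An adherence record kept for that arm alone identifies the arm to whoever takes it.
- Only controls are offered treatment at 12 weeks, so the offer identifies the other arm.
- The article names neither the recorder of adherence nor the person who makes the offer. It does not say whether either comes before or after the physical tests.

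**Step 5. What could disclose allocation at 6 months?** Outcomes and additional treatment are collected in one call, with no order given. The interviewer is not named. If it is the PI, the stated blind has lapsed. If it is someone else, nothing says that person is blind.

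**Count.** Of three follow-up contacts, one is clearly covered, one depends on the reading and on the visit order, and one is outside the stated blind.

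**The case against.** The strongest reply is that the sentence may simply be loose. Lifting the blind once the 12-week visit is complete fits both the general claim of blinding and the timing of the treatment offer. The adherence sentence is passive, so another person may take the record, or it may be taken last. Order within a visit is operational detail that an article often leaves to a fuller protocol or manual, and the schedule table is not visible here. The 6-month contact appears in neither the primary nor the secondary aims. By then controls have been offered treatment, so the randomised contrast is already diluted, and blinding the interviewer cannot restore it. Participants know their arm throughout.

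Most of this stands, and it limits the point. Four stronger readings are tempting and are not supported:

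- **That the 12-week physical measures are taken unblinded.** The text permits this but does not establish it. Neither the recorder of adherence nor the order of tasks is stated.
- **That the PI makes the 6-month calls knowing the arm.** No interviewer is named. What can be said is that the stated blind is over and no other blinded interviewer is described.
- **That the PI could predict new assignments.** The article says "The allocation sequence is concealed from the PI, who enrols and consents participants", and a reader might infer that learning earlier allocations from 12 weeks on weakens this. An independent colleague generated the sequence with randomly varied blocks of 4 and 6, and no accrual rate is given. Nothing shows that allocations in a block still being filled would be known.
- **That the primary result is compromised.** The 4-week endpoint lies inside the blinded period on either reading.

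What the reply does not remove is that the article states a rule, and on any reading that rule is narrower than the claim.

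**Conclusion.** The concern holds in a limited form. The unqualified assessor-blinded claim is supported at 4 weeks, uncertain for the examiner-dependent measures at 12 weeks, and unsupported by the stated rule at 6 months.

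The exposure is confined to outcomes after the primary endpoint, in up to the 64 planned participants. The 12-week physical measures matter most, because assessor blinding has most to protect there. For NDI, NPRS and GROC the benefit is only partial. The direction and size of any bias cannot be derived from the document.

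The verdict assumes that the PI is the examiner at follow-up, which the article strongly implies, and that no second blinded assessor is described in material not shown. It is a worthwhile, inexpensive improvement and does not threaten the main comparison.

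**What to change.** 1. Change the sentence under Randomisation so that the PI stays blinded to each participant's allocation until that participant's last outcome, the 6-month call, has been recorded. Name the 6-month interviewer and state whether that person is blinded.
2. At 12 weeks, complete range of motion, pressure pain threshold and ULNT 1 before any question on exercise adherence and before any offer of treatment is discussed.
3. Collect adherence at 12 weeks on a sealed form that the participant completes. Hand the same form to both arms, since a form given to one arm would itself disclose allocation.
4. At 6 months, record NDI, NPRS and GROC before asking about additional treatment.
5. For participants already assessed, or if the blind cannot be extended, limit the assessor-blinded description to the time points it covers.

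The cost is a revised sentence, a fixed visit and call order, one short form, and later unblinding of the PI. One item needs a check: if the PI now makes the 12-week offer to controls, a longer blind means that someone who already knows the allocation must make it. The article schedules no physiotherapist contact at 12 weeks, so passing this task to the physiotherapists could mean one extra brief contact per control participant.

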### Sample size estimation

The NDI and the NPRS are the independent primary outcome measures and sample size estimates were carried out for both outcome measures. An MCID for the NDI of 7 has been determined for cervical radiculopathy [48]. Using a reported NDI SD of 9.2 [48] for this patient group, with a two-sided 5% significance level and a power of 80%, a sample size of 29 participants per group is necessary. An MCID for the NPRS of 2 has been determined for mechanical neck pain, including cervical radiculopathy [43] and a SD of 1.85 [48]. Using these figures, with a two-sided 5% significance level and a power of 80%, a sample size of 15 per group was calculated. An online sample size calculator [49] for comparing means of 2 independent groups, that utilises reference tables [50] was used. The larger sample size per group calculated using the NDI was chosen and an additional 10% was added to account for anticipated dropout. In total, a sample size of 64 participants will be recruited.

### Data analysis plan

Baseline demographic characteristics and all outcome measures will be described and analysed using SPSS (IBM, version 24) or Stata statistical software (Statacorp LLC, Release 15). Descriptive characteristics will be presented for both groups following the CONSORT Statement. Data will be checked for normality using the Shapiro-Wilk test. Marginal effects will be used to calculate effect sizes for specified values for baseline differences. Results will be reported as mean differences between the groups and their 95% confidence intervals. Poisson regression will be used where data are non-parametric (Bland and Altman, 2011).

Statistical analysis will include two-way (treatment x time) ANOVAs and MANOVAs for between and within-group differences and interactions. Intention to treat analysis will be the primary approach employed. A per protocol analysis will also be undertaken and results compared to assess the impact of data that is not missing at random (NMAR) (Armijo-Olivo et al., 2009).

Secondary analysis will explore if any of the baseline outcome measures, symptom duration and group allocation are predictors of outcome (pain and disability) at 3 months. Appropriate multivariable regression analysis will be performed (linear or logistic).

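### The named treatment-by-time ANOVA compares change scores; adjusting each 4-week score for its own baseline is more precise, and for the NDI it may protect the stated power

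*Protocol article*

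**What the plan says.** The Data analysis plan section states that the analysis will include "two-way (treatment x time) ANOVAs and MANOVAs", covering differences between groups, differences within groups, and interactions. Results are to be given as mean group differences with 95% confidence intervals, and Poisson regression is the fallback for what the section calls non-parametric data. The Abstract likewise names ANOVAs and MANOVAs for the between-group comparison. No ANCOVA is named, and neither baseline NDI nor baseline NPRS is named as a covariate in the treatment comparison.

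One sentence bears on baseline: "Marginal effects will be used to calculate effect sizes for specified values for baseline differences". It does not say which model yields the marginal effects, which baseline variables are meant, or at what values.

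Outcomes are measured at baseline, 4 and 12 weeks, and the primary endpoint is at 4 weeks (Study design; Outcome measures). The Sample size estimation section uses a comparison of two independent means. For the NDI: "An MCID for the NDI of 7 has been determined for cervical radiculopathy", "Using a reported NDI SD of 9.2", and "with a two-sided 5% significance level and a power of 80%, a sample size of 29 participants per group is necessary". For the NPRS: "An MCID for the NPRS of 2 has been determined for mechanical neck pain, including cervical radiculopathy", "and a SD of 1.85", and "a sample size of 15 per group was calculated". The total is 64 after a 10% allowance for dropout.

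**The concern.** In a treatment-by-time ANOVA the baseline score is one of the outcome visits. The contrast that isolates the treatment effect at 4 weeks is the interaction between baseline and week 4, which is algebraically the group difference in mean change. The group main effect is no substitute: it averages in a visit at which randomisation makes the expected difference zero, and so dilutes the effect.

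The change score subtracts the whole baseline value, whatever its correlation with the later score. When that correlation is modest, this adds noise. ANCOVA estimates how much of the baseline to subtract and, apart from one degree of freedom, is never less precise than either the change-score comparison or the unadjusted 4-week comparison. It also deals with chance baseline imbalance, which the unadjusted comparison leaves in the result.

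At stake is the width of the primary confidence intervals in a trial of 64 and, under some assumptions, whether the NDI comparison has its stated power. Extra participants are not an easy remedy, because the Discussion reports that the initial recruitment strategies were insufficient.

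**Working it through.** **Inputs from Sample size estimation.** NDI: difference 7, SD 9.2, 29 per group. NPRS: difference 2, SD 1.85, 15 per group. Two-sided 5%, 80% power.

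**Assumed, not in the documents.** The correlation r between baseline and 4-week scores, shown over a range. For steps 2 to 4, the SDs are taken as single-visit SDs, equal at both visits; step 5 relaxes this for the NDI.

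**1. The plan's own figures reproduce.** Power is from the noncentral t distribution with 2n − 2 degrees of freedom and noncentrality difference / (SD × √(2/n)).
- NDI: 79.8% at 28 per group and 81.3% at 29, so 29 is the smallest n reaching 80%.
- NPRS: 78.6% at 14 per group and 81.5% at 15, so 15 is the smallest n reaching 80%.
- Dropout: 29 × 1.10 = 31.9, so 32 per group and 64 in total.

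**2. Variance of each comparison, relative to one visit.**
- Unadjusted 4-week score: 1
- Change score: 2(1 − r)
- 4-week score adjusted for baseline: 1 − r²

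The ratio of ANCOVA to change score is (1 − r²) / [2(1 − r)] = (1 + r)/2, that is 65% at r = 0.3, 75% at r = 0.5 and 85% at r = 0.7. Conversely, the change-score variance is larger by a factor of 2/(1 + r).

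**3. NDI at 29 per group.** The effective SD is 9.2 × √(2(1 − r)) for change and 9.2 × √(1 − r²) for ANCOVA.

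| r | Change SD | Change power | ANCOVA SD | ANCOVA power |
|---|---|---|---|---|
| 0 | 13.01 | 52.1% | 9.20 | 81.3% |
| 0.3 | 10.89 | 67.2% | 8.78 | 84.7% |
| 0.4 | 10.08 | 73.9% | 8.43 | 87.4% |
| 0.5 | 9.20 | 81.3% | 7.97 | 90.8% |
| 0.6 | 8.23 | 88.9% | 7.36 | 94.5% |
| 0.7 | 7.13 | 95.7% | 6.57 | 97.9% |

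The ANCOVA column ignores the one degree of freedom spent on the covariate. The unadjusted 4-week comparison has 81.3% at every r.

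The change score is noisier than a single visit exactly when r < 0.5. Because 29 per group gives slightly more than 80%, power crosses 80% at r of about 0.48. With all 32 per group retained it crosses at about 0.43. The normal approximation gives 0.47 and 0.41.

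The 95% half-width at r = 0.3 is t(56 df) × SD × √(2/29), with t = 2.003. That gives 5.73 NDI points for change, 4.84 unadjusted and 4.62 for ANCOVA.

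**4. NPRS at 29 per group.** Change-score power is 81.6% at r = 0 (82.9% by the normal approximation) and rises with r. No non-negative r takes it below 80%. The variance ratio (1 + r)/2 still applies, so the intervals are still wider than they need be.

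**5. If 9.2 is an SD of change.** Change-score NDI power is then 81.3% whatever r is. The ANCOVA SD becomes 9.2 × √((1 + r)/2), with power 94.2% at r = 0.3, 90.8% at r = 0.5 and 87.0% at r = 0.7.

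**The case against.** The strongest reply is that the article does not exclude baseline adjustment. Marginal effects at specified values come from a fitted model containing those values, and the list of ANOVAs is introduced as what the analysis will include, not as a complete list. This stands. A reader might infer that baseline enters only as a time level and that covariate adjustment is ruled out; the text does not support that. Nor does it state that adjustment would be triggered by observed imbalance. What it does is leave baseline's role open beside a named model in which baseline is an outcome.

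Second, a condensed article may leave covariate lists to an analysis plan that is not shown. That would answer a complaint about missing detail. The point here concerns the method the article does name, and a more precise one that uses the same data.

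Third, the planned contrast could be a plain between-group difference at 4 weeks, which fits the endpoint and the sample-size method and has 81% power at any r. That reading is open, and it would remove the NDI shortfall. It still gives up precision to ANCOVA whenever r differs from zero by more than the lost degree of freedom offsets.

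Fourth, a reader might infer a loss of power for both primary measures, or a threshold of exactly 0.5. Neither holds: the NPRS stays above 80%, and the NDI limit is somewhat below 0.5. The documents also do not establish that the correlation is low.

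**Conclusion.** The point holds as a matter of efficiency, not of bias: the treatment-by-time analysis is valid under randomisation. Its baseline-to-4-week contrast has 2/(1 + r) times the variance of a baseline-adjusted comparison, for both NDI and NPRS. This assumes equal SDs at the two visits, but not that the planning SDs are of one type or the other.

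A shortfall against the stated 80% is a narrower, conditional result. It concerns the NDI alone and requires that the interaction contrast is the primary estimate, that 9.2 is a single-visit SD, and that r is below about 0.48 at 29 per group (0.43 at 32). Under those conditions it can be material: 67% power at r = 0.3, against 85% with adjustment. The documents settle none of the three conditions. The change is worth making in any case, because it should improve precision at almost no cost.

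**What to change.** For each continuous outcome, make the primary estimate the 4-week group difference, with its 95% confidence interval, from a model that has that outcome's own baseline score as a prespecified covariate: baseline NDI for NDI, baseline neck NPRS for neck NPRS, and baseline arm NPRS for arm NPRS. Apply it whatever imbalance is observed. Do the same at 12 weeks and for the secondary measures that have a baseline value. Replace the sentence on marginal effects and baseline differences with this rule.

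The cost is a change of wording and one degree of freedom per model. The baseline scores are already collected, and the sample size need not change.

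### Poisson regression is named as the remedy for non-normal data, without a limit to counts or a robust variance; with default standard errors this could badly inflate type I error for the NDI

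*Protocol article*

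**What the plan says.** The relevant sentences are all in the protocol article, mostly in the Data analysis plan. Its first paragraph says "Data will be checked for normality using the Shapiro-Wilk test" and, after sentences on marginal effects and reporting, "Poisson regression will be used where data are non-parametric". No threshold is given for the normality test, and no outcome, type of data or variance estimator is attached to the Poisson sentence. The same paragraph says "Marginal effects will be used to calculate effect sizes for specified values for baseline differences" and "Results will be reported as mean differences between the groups and their 95% confidence intervals". The next paragraph sets out the main analysis: "Statistical analysis will include two-way (treatment x time) ANOVAs and MANOVAs for between and within-group differences and interactions".

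The outcomes, under Aims and Outcome measures, are the NDI and NPRS (primary), SF-12, HADS, FABQ, global rating of change, cervical range of motion, the ULNT 1 and pressure pain threshold (PPT). Sample size estimation gives the figures used below: "An MCID for the NDI of 7 has been determined for cervical radiculopathy" and "Using a reported NDI SD of 9.2", an NPRS MCID of 2 with SD 1.85, a two-sided 5% level and 80% power.

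**The concern.** The sentence treats Poisson regression as a way of handling data that are not normal. It is not one. It is a parametric count model, and its default standard errors are right only if the variance equals the mean. Summed questionnaire scores, 0-10 ratings, degrees of motion and pressures have no reason to meet that condition. If the variance exceeds the mean, default standard errors are too small, intervals too narrow and false positives too frequent. If it is smaller, the test is conservative.

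The rule carries no restriction on outcome, so it can reach the two primary measures at the 4-week endpoint. At stake is whether the two-sided 5% level used to size the trial would hold for disability. For a continuous measurement there is a further oddity. Multiplying the data by a constant c multiplies variance/mean by c, so the default Poisson p-value for PPT (load "applied at a rate of 30 kPa/sec") would depend on the unit of pressure.

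**Working it through.** **Plan's own figures.** The t-test calculation for a difference of 7 and SD 9.2 gives 28.1, so 29 per group. A difference of 2 with SD 1.85 gives 14.5, so 15. Then 2 × 29 = 58 and 58 × 1.1 = 63.8, so 64. All three reproduce, so the SDs can be taken as the plan's working values.

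**Inputs.** From Sample size estimation: NDI SD 9.2 (variance 84.64), NPRS SD 1.85 (variance 3.42), 29 per group. Assumed, because the article gives neither: NDI scored 0-50 with a mean of 10 to 30, and NPRS mean of 3 to 5.

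**Formula.** With n per arm and common mean m, the default Poisson standard error of the log ratio is √(2/(n·m)). The true one is about √(2·SD²/(n·m²)). Their ratio, true to default, is SD/√m, and n cancels. The real size of a nominal 5% test is therefore 2Φ(−1.96·√m/SD). For baseline adjustment, SD is replaced by SD·√(1−r²): 7.97 at r = 0.5 and 6.57 at r = 0.7.

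**NDI, single time point, default standard errors, fallback used:**

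| Assumed mean | Variance/mean | SE ratio | Size, unadjusted | r = 0.5 | r = 0.7 |
|---|---|---|---|---|---|
| 10 | 8.46 | 2.91 | 0.50 | 0.44 | 0.35 |
| 15 | 5.64 | 2.38 | 0.41 | 0.34 | 0.25 |
| 20 | 4.23 | 2.06 | 0.34 | 0.27 | 0.18 |
| 25 | 3.39 | 1.84 | 0.29 | 0.22 | 0.14 |
| 30 | 2.82 | 1.68 | 0.24 | 0.18 | 0.10 |

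The variance of 84.64 exceeds 50, the top of the assumed scale, so the unadjusted error is in the same direction at every possible mean. If the scale were 0-100 with a mean of 40, the size would be 0.18.

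**Simulation check** (29 per arm, 20,000 replicates, scores rounded and capped at 0-50, means 10 to 30):

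- Poisson always used, default standard errors: 0.49 to 0.22 with gamma-shaped data, 0.43 to 0.24 with normal data.
- Poisson with robust (sandwich) standard errors: 0.052 to 0.063.
- t-test: 0.046 to 0.052.

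**Whole two-stage rule** (4,000 replicates; Shapiro-Wilk in each arm, Poisson if either arm rejects at 5%, otherwise t-test; this trigger is an assumption). At means 10, 15, 20, 25 and 30 the size is 0.49, 0.36, 0.21, 0.15 and 0.08 for gamma-shaped data, and 0.34, 0.11, 0.07, 0.07 and 0.06 for near-normal data. The fallback is triggered in 99.5% down to 21% of trials with the former and 73% down to 8% with the latter.

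**NPRS, default standard errors.** Variance/mean is 1.14, 0.86 and 0.68 at means 3, 4 and 5, giving sizes of 0.067, 0.034 and 0.018. Simulation gives 0.066, 0.032 and 0.017.

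**PPT and range of motion.** The article gives no mean or SD, so no size can be computed.

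**The case against.** The strongest reply is that the article does not fix the variance estimator. Poisson estimation with sandwich standard errors is valid for means of non-negative outcomes, and the check above shows it near nominal. The choice of standard error is the kind of detail left to an analysis plan that is not at hand. This stands as a limit on the number, not on the point: the article states a rule, describes the method wrongly and leaves it open to every outcome.

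Four stronger readings are tempting and not supported:

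- *That the NDI analysis will have a false-positive rate of 25% to 50%.* That needs an assumed mean, default standard errors, no baseline adjustment and the fallback being used. The article settles none of these, and its mention of baseline differences suggests that adjustment is contemplated.
- *That a failed Shapiro-Wilk test is the stated trigger.* It is the natural reading, since no other criterion is offered, but other sentences separate the two statements and nothing links them. ANOVA and MANOVA remain the named main analysis.
- *That inflation affects both primary measures.* NPRS scores would often fail the normality test (73% to 98% of simulated gamma-shaped trials at means 5 to 3), but there the default model is near nominal to conservative. A high trigger rate for pain is no evidence of inflation for disability.
- *That the fallback abandons the promised mean difference.* The planned marginal effects can return mean differences from a log-link model. They do not repair default standard errors.

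**Conclusion.** The point holds in conditional form. The rule misdescribes Poisson regression and applies it without restriction to outcomes that are not counts. Its variance assumption is contradicted by the plan's own NDI SD on a 0-50 scale. If default standard errors are used and the fallback is invoked, the unadjusted NDI type I error is about 50% to 24% at assumed means of 10 to 30. It is lower, but still above 5%, with baseline adjustment (about 35% to 10% at r = 0.7). Over the whole two-stage rule it runs from about 49% to 6%, the low end being close to harmless. Robust standard errors remove nearly all of it. The NPRS would be near nominal to conservative (about 6.7% to 1.8%), so disability and pain would be held to different evidential standards under one rule. For PPT and range of motion the size of the effect cannot be stated from the document.

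**What to change.** Delete the Poisson fallback for scale and continuous outcomes. Keep one pre-specified baseline-adjusted linear model for each, reporting the mean difference with its 95% confidence interval whatever the normality test shows, with robust or bootstrap intervals if residuals are clearly non-normal. If Poisson regression is to stay, the minimum is to restrict it to true counts, or to require robust (sandwich) variance and say which outcomes it serves and what triggers it. The cost is analysis wording only; neither the data collected nor the sample size of 64 changes.
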